### 4.5. Pregnancy Outcomes

Information about adverse pregnancy outcomes will be collected from prenatal and delivery records, including excessive GWG or insufficient GWG, insulin use during pregnancy, cesarean section, premature delivery, macrosomia, and fetal growth restriction.

## 5. Data Collection

Data will be collected by a specially-assigned person who is unaware of participant allocation and intervention content.

## 6. Statistical Analysis

All quantitative analysis will be conducted through IBM SPSS Statistics 24.0 software (IBM Corp. Released 2016. IBM SPSS Statistics for Windows, Version 24.0., IBM Corp.: Armonk, NY, USA). The baseline characteristics of participants will be presented by descriptive statistics. The continuous variables will be described by means and standard deviation, or medians and quartiles. The frequencies (N) and percentages (%) will be used for categorical variables. The analysis of variance (ANOVA), Kruskal–Wallis, test or Chi-square test will be used to describe the mean differences of continuous variables and categorical variables between the two groups at baseline. The explored assessment will be analyzed by repeated measures multivariate analysis of variance (MANOVA), and then the post-hoc pairwise comparison will be made. Effect sizes were calculated with Cohen’s d. P value of 0.05 will be considered the significant level for all outcomes.

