**Compliance with Dietary recommendations**						
Self-management behavior				√		
Self-efficacy				√		
Average daily GL value			√	√		

Abbreviations: 75 g OGTT, 75 g oral glucose tolerance test; FBG, fasting blood glucose ; 2 h BG, 2 h postprandial blood glucose; GL, glycemic load.

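### Repeated measures MANOVA, the only outcome analysis named, cannot be run on two of the three primary outcomes because Table 2 schedules them once, and for average daily GL the tested term is not stated

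*Protocol article*

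**What the plan says.** Section 6 (Statistical Analysis) gives one sentence on outcome analysis: "The explored assessment will be analyzed by repeated measures multivariate analysis of variance (MANOVA"; the same sentence adds pairwise comparisons afterwards. What the sentence takes as its object is not defined. The other tests in that section (ANOVA, Kruskal–Wallis, chi-square) are tied to baseline; they "will be used to describe the mean differences of continuous variables and categorical variables between the two groups at baseline". On effect sizes it says "Effect sizes were calculated with Cohen’s d", and on significance "P value of 0.05 will be considered the significant level for all outcomes".

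Section 4 (Measures) lists three primary outcomes: self-management behaviors, self-efficacy of dietary control, and the average daily GL value. It refers to Table 2 for timing. In Table 2 the row "Self-management behavior" and the self-efficacy row each carry one tick, at 37 weeks. The row "Average daily GL value" carries two, at 28 and 37 weeks. None of the three is ticked at enrollment, and Section 4.2 lists only demographic and pregnancy-related questionnaires at baseline.

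Section 4.5 takes the pregnancy outcomes from records: gestational weight gain outside the normal range, and "insulin use during pregnancy, cesarean section, premature delivery, macrosomia, and fetal growth restriction". Section 3.5 describes a pilot with 30 women per group, whose results will be used to size a later study.

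**The concern.** The named method and the measurement schedule do not fit each other. A repeated measures analysis needs each outcome on at least two occasions, and two of the three primary outcomes have one. Those two scores are also the whole of the first hypothesis in Section 2.

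For GL the method can be run, but both occasions follow randomisation. In such a model the group main effect and the group-by-time interaction answer different questions, and the plan does not choose between them. An analyst who took the interaction as the test would be asking only whether the difference between arms changed from 28 to 37 weeks.

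The missing enrollment values matter for a pilot in a second way. Without them it cannot estimate the correlation between enrollment and 37 weeks that a later trial would need if it were sized for a baseline-adjusted analysis.

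**Working it through.** The plan gives no effect size, SD or power, so there is no figure of its own to reproduce.

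**Step 1. Occasions and within-subject contrasts.** With t occasions there are t − 1 time contrasts. From Table 2:

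| Outcome | Occasions | t | t − 1 |
|---|---|---|---|
| Self-management behavior (primary) | 37 weeks | 1 | 0 |
| Self-efficacy (primary) | 37 weeks | 1 | 0 |
| Average daily GL (primary) | 28 and 37 weeks | 2 | 1 |
| FBG, 2 h PBG, HbA1c (secondary) | one week after enrollment, 37 weeks | 2 | 1 |

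Section 4.4 gives study entrance in place of one week for the glucose measures, but the count is two either way. The two primary scores have zero time contrasts, so there is nothing repeated to model. Nor can the three primary outcomes be modelled jointly over time, since the only occasion they share is 37 weeks.

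**Step 2. Is a comparison without baseline valid?** A MANOVA of the two scores at 37 weeks alone is a Hotelling T² test between arms. It was simulated under no effect with 30 per arm, an assumed correlation of 0.5 between the scores, and 20,000 runs. Type I error was 0.049 against a nominal 0.05, so the randomised comparison is sound.

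**Step 3. GL: which term?** Suppose the intervention shifts GL by the same amount, d SD, at both visits. The interaction compares the arms on (37-week value − 28-week value), where the expected difference is d − d = 0. Its power is therefore the alpha level. The main effect compares the arms on the mean of the two visits, where the expected difference is d. Simulated with d = 0.8 (assumed), 30 per arm, 20,000 runs:

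| Within-person correlation (assumed) | Power, group-by-time | Power, group main effect |
|---|---|---|
| 0.3 | 0.050 | 0.965 |
| 0.5 | 0.050 | 0.941 |
| 0.7 | 0.050 | 0.913 |

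**Step 4. Cost of having no enrollment value.** Adjusting for an enrollment value that has correlation r with the 37-week value multiplies the variance by 1 − r². The equivalent sample size per arm is 30/(1 − r²). Without adjustment, the standardised difference detectable with 80% power at two-sided 0.05 is (1.960 + 0.842) × √(2/30) = 0.72. With adjustment it is 0.723 × √(1 − r²).

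| r (assumed) | 1 − r² | 30 per arm acts as | Detectable difference (SD) |
|---|---|---|---|
| 0.3 | 0.91 | 33 | 0.69 |
| 0.5 | 0.75 | 40 | 0.63 |
| 0.7 | 0.51 | 59 | 0.52 |

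**The case against.** The strongest reply is that this is a condensed article about a pilot, and that a fuller protocol or SAP may name other tests. That would answer a silence. Here, though, the article states a method and a schedule that contradict each other, and no later document can recover enrollment values that were not collected.

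The remaining objections limit how far the point goes, and most of them stand:

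- A reader might infer that the primary comparison is invalid, or that chance imbalance will be mistaken for an effect. Neither follows. Under randomisation the p value and confidence interval already allow for chance imbalance, and Step 2 shows a valid test at 37 weeks.
- A reader might infer that the GL analysis is bound to miss a constant benefit. It would do so only if group-by-time were the test, and Section 6 names no term.
- A reader might think pairwise comparisons are empty with two arms. By-visit comparisons of the arms are a proper follow-up for GL, FBG, 2 h PBG and HbA1c.
- A reader might infer that MANOVA and Cohen's d are assigned to the pregnancy outcomes. Section 6 does not say so. Those outcomes are secondary and do not touch the primary comparison.
- The gain from an enrollment score may be small for self-management. Some items in Section 4.3 ask about behaviours, such as consulting GL values, that are taught only at enrollment, so early answers may lie near zero. The case is stronger for self-efficacy.
- An enrollment GL value would need the three-day record of Section 4.3, while Section 3.6 enrolls women as soon as they consent.
- Separate analyses give up a joint test. Three independent tests at 0.05 have a familywise error of 1 − 0.95³ = 0.14. Section 6 already applies 0.05 to every outcome, so the change does not create this, and a pilot meant to estimate effects should rest on intervals.

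**Conclusion.** The point holds as a mismatch between Section 6 and Table 2. The named method is not executable for two of the three primary outcomes and is ambiguous for the third. The randomised comparison itself remains valid, and a 37-week difference with its effect size can be obtained from the planned data.

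For GL, the choice of term could move power from above 0.9 to 0.05 if the effect is constant and near 0.8 SD. Having no enrollment values is a loss of precision, equivalent to forgoing 3 to 29 women per arm (33 − 30 to 59 − 30) for r between 0.3 and 0.7. Neither that range nor the 0.8 SD comes from the documents. The conclusion also rests on the position of the ticks in Table 2, and on the MANOVA sentence covering the primary outcomes. The second is an inference, but no other outcome method is offered.

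**What to change.** 1. **The two scores.** Add the 5-item self-management questionnaire and the 9-item self-efficacy subscale to the Enrollment column of Table 2, completed before allocation is revealed and before any dietary teaching. Analyse each 37-week score by ANCOVA on arm and its enrollment value, and report the adjusted difference with a 95% CI. If the enrollment items are not added, at minimum name a between-group comparison at 37 weeks.
2. **GL.** State that the test is the difference between arms (group main effect, or the 37-week difference) and not group-by-time. An enrollment GL value is optional.
3. **Pairwise comparisons.** Keep them, by visit, for outcomes measured repeatedly.
4. **Pregnancy outcomes (secondary).** Report binary outcomes as risk differences with 95% CI, without Cohen's d.

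The cost is a rewrite of part of Section 6 and a few minutes for 14 items at a visit that already takes place. The enrollment items must be in place before recruitment; the other changes need no new data.

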## 2. Research Hypothesis

We hypothesize that after the intervention, women with GDM who receive the intervention program designed based on BCW will have (1) higher scores of self-management behavior and self-efficacy, (2) better results of maternal glucose metabolism, and (3) lower incidences of common adverse pregnancy outcomes than women with GDM who receive general dietary management.

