### 3.5. Sample Size

Due to the lack of prior data about applying BCW in dietary intervention in women with GDM, a pilot study will be carried out to provide a comprehensive estimate of the effect size of the intervention. The recruitment goal of the pilot study is 30 pregnant women with GDM for each group [29]. No a priori hypotheses of effect size to identify the ineffectiveness of a comprehensive study were proposed since we considered that the available data were insufficient to create these meaningfully. The minimum sample size for the future study will be calculated based on the results of the pilot study.

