### 3.6. Recruitment

Participants will be recruited when pregnant women return to the obstetrics clinic for their 75 g OGTT results. Obstetricians will explain the purpose and significance of this study and emphasize that the trial will be conducted in strict confidentiality. Women with GDM who volunteer to participate in this study will be enrolled immediately after signing the informed consent forms.

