### 3.7. Randomization and Blinding

Researchers will use the study website (www.random.org/lists/, (accessed on 19 May 2022)) to create random numbers that correlate to the serial numbers before recruiting participants. The ratio of random allocation is 1:1. Eligible participants will be sequentially recruited and assigned the predetermined random number. Participants with a random number of 1–30 will be divided into the dietary intervention group based on BCW (intervention group), while those with a random number of 31–60 will be divided into the general dietary management group (control group). In this study, participants and interveners will inevitably know the content of the intervention. Therefore, researchers will only ensure the separation of interveners and result assessors.

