### 4.4. Maternal Glucose Metabolism Measurement

The laboratory department of the hospital will be responsible for measuring the experimental indicators related to maternal glucose metabolism. The experimental indicators include OGTT, FBG, 2 h PBG, and HbA1c, which will be measured at the study entrance and again at 37 weeks of gestation. Data on the results of these experimental indicators will be collected from the prenatal and delivery records of participants.

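### The glucose outcomes are analysed without adjustment for a pre-allocation value the trial already collects, which costs precision at 30 per arm; the size of the loss depends on assumptions and on an unresolved measurement schedule

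*Protocol article*

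**What the plan says.** Section 2 states a between-arm glucose hypothesis, "2) better results of maternal glucose metabolism", and section 4 lists the glucose measures as secondary outcomes.

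Section 6 gives the outcome analysis in one sentence: "The explored assessment will be analyzed by repeated measures multivariate analysis of variance (MANOVA), and then the post-hoc pairwise comparison will be made". It does not list the time points, define which outcomes are meant, or say which term of the model is decisive. The only stated use of baseline data is descriptive statistics and tests that "will be used to describe the mean differences of continuous variables and categorical variables between the two groups at baseline". The threshold is general: "P value of 0.05 will be considered the significant level for all outcomes".

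On when glucose is measured, the article gives three statements:
- **Section 3.6:** "Participants will be recruited when pregnant women return to the obstetrics clinic for their 75 g OGTT results". The OGTT therefore precedes allocation, and Table 2 ticks it at enrollment.
- **Section 4.4:** OGTT, FBG, 2 h PBG and HbA1c, "which will be measured at the study entrance and again at 37 weeks of gestation".
- **Table 2:** FBG, 2 h PBG and HbA1c at one week after enrollment and at 37 weeks, with no tick at enrollment. The OGTT is ticked at enrollment only.

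On size, section 3.5 says: "The recruitment goal of the pilot study is 30 pregnant women with GDM for each group". It proposes no effect size, states no power, and says the pilot results will be used to size the future study.

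**The concern.** A pre-allocation measurement of an outcome usually serves best as a covariate. In a two-time-point repeated measures model it becomes a second response instead. None of the between-arm contrasts such a model offers is then the baseline-adjusted one:
- The group-by-time term is a comparison of change scores.
- The group main effect averages in an entry value on which the intervention cannot have acted.
- A pairwise comparison at 37 weeks does not use the entry value.

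With 60 women and an effect estimate intended to size a later trial, precision is what this pilot has to deliver. Wider intervals for FBG, 2 h PBG and HbA1c would pass directly into that later calculation.

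**Working it through.** The article states no power, effect size or calculated sample size, so there is no figure to reproduce.

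**Inputs from the article**
- n = 30 per arm (section 3.5); "The ratio of random allocation is 1:1" (section 3.7).
- Significance level 0.05 (section 6).
- Entry and 37 weeks as the two time points (section 4.4).

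**Inputs assumed**
- Two-sided testing, because sidedness is not stated.
- d, the true difference in units of the 37-week SD: reference 0.5, range 0.3 to 1.0.
- rho, the correlation between entry and 37-week values: 0.3, 0.5 and 0.7, wider range 0.2 to 0.8.
- Equal SDs at the two times (relaxed in step 4), and no dropout.

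**Step 1. Variance of each contrast, in units of the 37-week variance**
- Change score (group-by-time): 2(1 − rho).
- Unadjusted 37-week comparison: 1.
- ANCOVA on the entry value: 1 − rho².
- Group main effect: it estimates d/2, with variance (1 + rho)/2.

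**Step 2. Sample-size penalty, which does not depend on d**

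Change score against ANCOVA: 2(1 − rho)/(1 − rho²) = 2/(1 + rho).
- rho 0.3: 2/1.3 = 1.54
- rho 0.5: 2/1.5 = 1.33
- rho 0.7: 2/1.7 = 1.18

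**Step 3. Power at n = 30 per arm and d = 0.5**

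Noncentral t with noncentrality (effect/√variance) × √(30/2), on 58 degrees of freedom (57 for ANCOVA).

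| | rho 0.3 | rho 0.5 | rho 0.7 |
|---|---|---|---|
| Group-by-time (change score) | 36.3% | 47.8% | 69.1% |
| Unadjusted at 37 weeks | 47.8% | 47.8% | 47.8% |
| Group main effect | 21.9% | 19.6% | 17.8% |
| ANCOVA | 51.4% | 59.4% | 76.0% |
| ANCOVA minus group-by-time (points) | 15.1 | 11.6 | 6.9 |
| ANCOVA minus unadjusted (points) | 3.6 | 11.6 | 28.2 |

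Simulation at d = 0.5 and rho = 0.5 gave similar results: a loss of 10.8 points for a single outcome, and 9.9 points for three outcomes tested jointly (MANOVA on change against MANCOVA).

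**Step 4. Sensitivity**
- *Effect size.* At d = 0.3 the loss against group-by-time is 6.2 points (rho 0.3) to 4.5 points (rho 0.7). At d = 1.0 it is 8.3 to 0.1 points. Over d from 0.3 to 1.0 and rho from 0.2 to 0.8 it runs from about 0 to just over 21 points.
- *Unequal SDs.* If the entry SD is k times the 37-week SD, the change-score variance is 1 + k² − 2·rho·k. At k = 0.7 this is 1.07, 0.79 and 0.51 at rho 0.3, 0.5 and 0.7, against ANCOVA's 0.91, 0.75 and 0.51. The gain shrinks to about 6, 2 and 0 points. At k = 1.4 and rho = 0.7 the change-score variance is 1.00 against 0.51, and the gain is about 28 points.

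**Step 5. If Table 2 is the true schedule**

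The two repeated values of FBG, 2 h PBG and HbA1c would then be at one week and 37 weeks, both after allocation. The one-week value also follows the primary consultation and the three-day online consultation, so it may already carry some treatment effect. The figures in steps 2 to 4 do not apply on this schedule. The OGTT fasting and 2 h values would still be available before allocation and unused. HbA1c would have no pre-allocation value.

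**The case against.** The strongest reply is that this is a matter of efficiency and not validity. Under randomisation, change-score and 37-week contrasts are unbiased without adjustment, and chance imbalance at entry is already reflected in their standard errors. The outcomes are secondary, the trial is a pilot, and no power was promised. All of that stands.

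It is also fair to say that section 6 does not identify its time points, and that on Table 2 no entry value of FBG, 2 h PBG or HbA1c exists to be a repeated response. That stands too. The entry value being treated as a response is an inference that holds under section 4.4 only.

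A reader might infer that the plan loses a definite 7 to 15 points of power. The article does not support this: it gives neither d nor rho, and that range needs d = 0.5, rho from 0.7 down to 0.3 and equal SDs. Nor is ANCOVA better in every case. At this sample size and a very low correlation (0.05 to 0.1 in simulation) its variance was slightly above that of the unadjusted comparison, and with an entry SD of 0.7 of the 37-week SD and rho near 0.7 it gains nothing over change scores.

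One reply does not carry: that covariates are a detail left to a document not shown. Section 6 names the method and states how baseline data are used, so this is a choice already made and not a gap.

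**Conclusion.** The point holds as an efficiency improvement. Section 6 fixes an outcome analysis with no baseline covariate while the trial already collects pre-allocation glucose values: the OGTT on either schedule, and like-for-like entry values under section 4.4.

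Under the section 4.4 schedule with equal SDs, reading the group-by-time test costs the equivalent of 18% to 54% more women for rho from 0.7 to 0.3. The corresponding loss of power is conditional on the assumed effect size and SD ratio. No missed power figure and no bias follow. What follows is a wider interval around the estimates meant to size the later trial.

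The baseline significance tests in section 6 are not part of this point; dropping them would be a reporting preference.

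**What to change.** 1. Reconcile section 4.4 with Table 2 on when FBG, 2 h PBG and HbA1c are first measured. The covariate cannot be fixed until this is settled.
2. In section 6, compare each 37-week glucose outcome between arms by ANCOVA, with arm as factor and the pre-allocation value of the same measure as covariate where it exists.
3. Where it does not exist, use the enrollment OGTT fasting value for FBG and the OGTT 2 h value for 2 h PBG. These are weaker covariates: women were selected on OGTT thresholds, and the 2 h value follows a glucose load and not a meal. Expect a smaller gain than in the table above.
4. If HbA1c has no pre-allocation value, compare it at 37 weeks without adjustment for baseline HbA1c.
5. Do not use the one-week value as covariate, because it is taken after allocation and after the first consultations.
6. Report the adjusted mean difference with a 95% CI.

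Cost: one sentence in section 6 and one residual degree of freedom per adjusted outcome. No new visits or data are needed, and the planned software can fit the model.

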### 3.4. Participant Shedding Criteria

In the following cases, participants will be withdrawn if: (1) Pregnant women who opt to terminate their pregnancy during the study period, (2) pregnant women who do not wish to continue to participate in the study, (3) pregnant women who have difficulties in continuing to participate in this study due to the following physical conditions that happen during the intervention process, such as vaginal bleeding, threatened premature delivery, placental abnormalities.

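### Repeated-measures MANOVA keeps only women complete on every value in the model, so for outcomes measured twice a woman without a 37-week value is dropped although an earlier value exists

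*Protocol article*

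**What the plan says.** Section 6 names one method for the follow-up data, with pairwise comparisons to follow it: "The explored assessment will be analyzed by repeated measures multivariate analysis of variance (MANOVA". The software is fixed ("All quantitative analysis will be conducted through IBM SPSS Statistics 24.0 software"), and effect sizes are to be expressed as Cohen's d. The section does not say whether several outcomes enter one model or each outcome has its own.

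Table 2 sets these follow-up times:

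| Outcome | Role (section 4) | Times ticked |
|---|---|---|
| FBG, 2 h PBG, HbA1c | secondary | one week after enrolment, 37 weeks |
| Average daily GL | primary | 28 weeks, 37 weeks |
| Self-management, self-efficacy | primary | 37 weeks only |

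For the glucose measures, section 4.4 gives a different first time: "which will be measured at the study entrance and again at 37 weeks of gestation". Both places agree on 37 weeks as the last.

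Section 4 lists premature delivery as a secondary outcome. Section 3.4 withdraws women who have difficulty continuing because of conditions "such as vaginal bleeding, threatened premature delivery, placental abnormalities". Section 4.5 takes the adverse pregnancy outcomes from prenatal and delivery records.

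Section 3.5 describes the study as a pilot of 30 women per group whose results will set the size of a later trial.

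**The concern.** Classical repeated-measures MANOVA works on one vector of values per woman. If any element is missing, the woman leaves that model and her observed values go with her. Every outcome that Table 2 ticks twice has its second value at 37 weeks, so a woman who has delivered or been withdrawn by then contributes nothing to that analysis.

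These women are unlikely to be a random subset. Delivery before 37 weeks bears directly on a listed outcome, and threatened premature delivery is a listed reason for withdrawal. Section 2 also expects the intervention to lower adverse pregnancy outcomes, so the losses could differ between arms.

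What is at stake is the product of the pilot. A Cohen's d computed on completers is less precise, and possibly biased, and it would be carried into the sample size of the next trial. For the two primary outcomes with a single measurement there is nothing repeated to analyse, so the stated method does not fit them.

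**Working it through.** **No figure to reproduce.** The 30 per group is a cited pilot size. Section 3.5 gives no effect size, standard deviation, power or dropout rate ("No a priori hypotheses of effect size to identify the ineffectiveness of a comprehensive study were proposed").

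**Inputs.** From the document: 60 women, 1:1 allocation, and the Table 2 visits. Assumed, because the document gives none: a missing rate m of 2%, 5% or 10% per value, independent between values, and a rate p of delivery before 37 weeks of 5%, 10% or 15%.

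**1. Behaviour of the method.** A MANOVA run in statsmodels (not SPSS) on 60 simulated rows, with one missing value in each of 5 rows, kept 55 rows. This is listwise deletion.

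**2. One outcome at two visits.** Complete women = 60 × (1 − m)². The women lost are of three kinds: only the 37-week value missing, 60 × m(1 − m); only the earlier value missing, the same number; both missing, 60 × m².

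| m | Complete | Lost | Only 37-week value missing | Only earlier value missing | Both missing |
|---|---|---|---|---|---|
| 2% | 57.6 | 2.4 | 1.2 | 1.2 | 0.02 |
| 5% | 54.1 | 5.9 | 2.85 | 2.85 | 0.15 |
| 10% | 48.6 | 11.4 | 5.4 | 5.4 | 0.6 |

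A model on all available values keeps everyone except the last column.

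**3. Three glucose measures modelled jointly (6 values).** Complete women = 60 × (1 − m)⁶ = 53.2, 44.1 and 31.9, so 6.8, 15.9 and 28.1 are lost. Independence makes this an upper range. If the three laboratory values at a visit are always missing together, only two visits matter and the loss returns to that of step 2.

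**4. Visit-based rates.** Assume 5% miss the first visit, 15% miss 37 weeks, and 2% of values are lost sporadically.
- One outcome at both visits: 0.95 × 0.85 × 0.98² × 60 = 46.5 women.
- The 37-week value alone: 0.85 × 0.98 × 60 = 50.0 women.
- Loss due to requiring both values: about 3.5 women.
- Joint model of six values: 0.95 × 0.85 × 0.98⁶ × 60 = 42.9 women, about 7 fewer than 50.

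**5. Early delivery alone.** Expected loss = 60 × p = 3, 6 or 9 women. The chance of losing at least one, 1 − (1 − p)⁶⁰, is already 95% at p = 5%.

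**6. Precision.** The standard error of an arm difference goes with 1/√n.
- Against all 60 women, one outcome at two visits inflates it by 1/(1 − m) = 1.02, 1.05 and 1.11.
- Against an analysis of the 37-week value alone, which keeps 60 × (1 − m), the inflation is 1/√(1 − m) = 1.01, 1.03 and 1.05.
- The joint six-value model, against all 60, gives 1/(1 − m)³ = 1.06, 1.17 and 1.37.

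**The case against.** **The joint model is not stated.** A reader might infer that one missing HbA1c removes a woman's FBG and 2 h PBG as well. Section 6 does not settle this, since repeated-measures routines also give multivariate tests for one outcome over time. The objection stands: joint-model losses are conditional. The loss within a single outcome remains.

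**The number lost is assumed.** A reader might infer that the trial will lose many women. The document gives no missing, dropout or preterm rate, so no number can be derived from it. For one outcome at two visits the loss of precision due to the method alone is small (step 6). This stands.

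**Early deliveries are not lost to the trial.** A reader might infer that they disappear altogether. They do not. The adverse pregnancy outcomes come from records and need no 37-week visit, and several are binary and would not go through MANOVA.

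**MANOVA is not the cause everywhere.** Self-management and self-efficacy have only a 37-week tick, so a woman without that visit is lost under any analysis of observed values. This stands. What remains is that a repeated-measures method does not fit these two outcomes.

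**The glucose point depends on timing.** If section 4.4 is followed and the first glucose value is taken at entry, it is a baseline, and a woman with only that value says little about the 37-week difference. This stands for the glucose measures. Average daily GL is unaffected, because both its values follow enrolment.

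**Missing-data handling may be in a plan not shown.** True, and its absence is not criticised here. The point concerns the method the article does fix, which is complete-case unless values are filled in first.

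**There is no power target.** True. The harm is to the effect estimate.

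**Conclusion.** The point holds in limited form. For average daily GL and, on Table 2's timing, for FBG, 2 h PBG and HbA1c, the stated method discards earlier values of women who lack a 37-week value, and 37-week values of women who missed the earlier visit. Those without a 37-week value include women who deliver or are withdrawn early, so the loss may be related to prognosis. The direction and size of any bias cannot be told from the document. For self-management and self-efficacy the method is unsuited to a single measurement.

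Under assumed, independent missingness of 2% to 10% per value, about 2 to 11 of 60 women are lost for one outcome at two visits. The joint three-measure model loses up to 7 to 28, if outcomes are modelled together and values go missing independently. This is a modest but real weakness in a pilot whose purpose is an effect estimate, and it should be changed.

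**What to change.** Replace the MANOVA sentence in section 6 with one analysis per continuous outcome:

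- **Two follow-up visits:** a linear mixed model (REML, unstructured covariance, arm by visit) including every randomised woman with at least one value.
- **One follow-up visit:** ANCOVA.
- **Adjustment:** use a baseline value where one is collected at entry, for example the OGTT glucose values. Table 2 ticks no entry value for self-management or self-efficacy, so those two have no baseline score to adjust for as scheduled.
- **Estimate:** report the 37-week difference between arms, with its confidence interval, as the effect size for planning.

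Reconcile section 4.4 with Table 2 on the first glucose measurement, since this decides which of the two models applies to those outcomes.

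The cost is wording only, and the MIXED procedure in SPSS fits the model. Several outcome-specific estimates replace one omnibus test. The mixed model reduces bias only if values are missing at random given what was observed, and it cannot recover outcomes measured only at 37 weeks.
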